## Abstract

**Background:**

Perioperative chemotherapy (ChT) and preoperative chemoradiation (CRT) are both the standard treatments for locally advanced gastric cancer (LAGC). CRT can achieve a higher pathological complete regression (pCR) rate, but whether this higher pCR rate can be transformed into a long-term survival benefit remains inconclusive. Therefore, relevant studies are in progress. On the other hand, immunotherapy has been established for the first-line treatment of advanced gastric cancer (AGC) and has been widely explored in the perioperative setting. The combination of chemotherapy/radiotherapy and immunotherapy may have a synergistic effect, which will lead to a better antitumor effect. The preliminary reports of ongoing studies show promising results, including a further improved pCR rate. However, the preferred treatment combination for LAGC is still not established. To solve this problem, we are carrying out this randomized phase II trial, which aims to evaluate the efficacy and safety of perioperative chemotherapy plus the use of PD-1 antibody with or without preoperative chemoradiation for LAGC.

**Methods:**

Eligible patients with LAGC or gastroesophageal junction (GEJ) adenocarcinoma were randomized to receive perioperative ChT, PD-1 antibody, surgery with (Arm A) or without preoperative CRT (Arm B), and PD-1 antibody maintenance until one year after surgery. The primary endpoint of this study is that the pCR rate of Arm A will be significantly higher than that of Arm B. The secondary endpoints include the pathological partial regression (pPR) rate, R0 resection rate, objective response rate (ORR), event-free survival (EFS), overall survival (OS), safety and surgical complications. Moreover, several explorative endpoints will be evaluated to find and validate the predictive biomarkers of immunotherapy.

**Discussion:**

The results of the NeoRacing study will provide important information concerning the application of PD-1 antibody in LAGC patients during the perioperative setting. Meanwhile, the two treatment protocols will be compared in terms of efficacy and safety.

**Trial registration:**

ClinicalTrials.gov, NCT05161572. Registered 17 December 2021 - Retrospectively registered.

## Background

According to the recently updated GLOBOCAN 2020, gastric cancer (GC) ranks fifth and fourth in terms of the estimated number of new cases and the number of deaths worldwide, respectively [1]. Of note, the majority of the worldwide GC cases and deaths occur annually in China, accounting for 43.9% of the worldwide cases and 48.6% of the worldwide deaths [1]. In this large GC patient population in China, locally advanced gastric cancer (LAGC) accounts for approximately 70.8% of the cases [2]. Therefore, how to appropriately treat these patients and improve their survival is a serious challenge.

The main treatment of LAGC is surgery-based multidisciplinary therapy [3]. Perioperative ChT and preoperative CRT are both recommended for LAGC in the NCCN guidelines for GC. High-level evidence of preoperative CRT has been mainly found for GEJ tumors [4, 5], but there is relatively rare evidence for its use in middle and distal GCs. Therefore, perioperative ChT obtains a higher recommendation level than preoperative CRT for LAGC. Both of these therapies have been proven safe and effective [6–8]. Compared with perioperative ChT, preoperative CRT can achieve better short-term efficacy, such as by achieving a higher pCR rate and a decreased tumor stage [9]. However, whether this benefit can be transformed into a long-term survival benefit is unknown [10]. Several ongoing randomized controlled trials from the East and the West, such as the PREACT (NCT03013010) [11], Neo-CRAG (NCT01815853), TOPGEAR (NCT01924819) [12] and CRITICS-2 (NCT02931890) [13], are trying to provide the answer.

In 2012, a phase 2 trial (NCT02024217) was designed and conducted at our center, and this study aimed to evaluate the efficacy and safety of preoperative CRT for LAGC [8]. Due to the promising results observed in our phase 2 trial, a phase 3 randomized trial called PREACT (NCT03013010) was launched in 2017, which aimed to compare the efficacy of preoperative CRT with preoperative ChT for LAGC [11].

Major advances with immune checkpoint inhibitors (ICIs) have started to change the clinical practice (especially for the treatment and prognosis) for GC. With the publication of the results of the CheckMate-649 study and the ATTRACTION-4 study, ICIs have been successfully established as a first-line treatment for advanced gastric cancer (AGC). Clinical trials of ICIs combined with chemotherapy, radiotherapy and/or targeted therapies in the perioperative setting are being carried out. Available research data has shown that with the addition of ICIs in the neoadjuvant setting, the pCR rate can be substantially improved.

Tegafur gimeracil oteracil potassium capsule (S-1) plus oxaliplatin (SOX regimen) is the preferred ChT regimen in East Asian countries. The preliminary results of two large-scale randomized trials (RESOLVE [14], RESONANCE [15]) in China suggested that the neoadjuvant SOX regimen is beneficial in terms of the R0 resection rate, tumor shrinkage and survival prolongation. Patients in the neoadjuvant chemotherapy group achieved a longer DFS than patients in the control group. Moreover, the efficacy and safety of the SOX regimen plus CRT have been proven by our previous trials [8]. Therefore, in this study, we continued to use the SOX regimen. Sintilimab is a fully human IgG4 monoclonal antibody (mAb) that is registered as Tyvyt. It was developed by Innovent Biologics and Eli Lilly and Company [16]. In the Orient-16 trial (NCT03745170), sintilimab plus capecitabine/oxaliplatin significantly improved the OS and PFS in patients with gastric/GEJ adenocarcinoma, regardless of the PD-L1 expression. As sintilimab has a similar antitumor effect as nivolumab and pembrolizumab, has a better safety profile and has obvious economic advantages, we decided to use sintilimab in our study.

Positive peritoneal lavage cytology without visible gross peritoneal metastasis (CY1P0) is a special type of distant metastasis of GC, which is defined as stage IV disease in the American Joint Committee on Cancer (AJCC) guidelines for GC (8th edition) [17] and in the Japanese Classifications of Gastric Carcinoma [18]. It has been reported to be a key predictor of peritoneal dissemination [19] and poor prognosis [20–23]. Currently, the therapeutic strategies for GC with CY1P0 have not been fully defined [24]. Typically, palliative chemotherapy has been widely accepted as the standard therapy for stage IV GC patients globally [25, 26]. Moreover, curative-intent surgery was not indicated in GC patients with CY1 according to the treatment algorithm in the Japanese gastric cancer treatment guidelines [25]. However, radical surgery followed by postoperative chemotherapy is one of the most widely accepted therapeutic strategies for GC patients with CY1 in clinical practice and was established by a phase II trial called the CCOG0301 study [27, 28]. In addition, preoperative chemotherapy as an initial treatment for GC patients with CY1 is considered a promising treatment strategy, as systemic chemotherapy could eliminate the limited metastatic disease in some patients, could convert the metastatic disease to resectable disease and could achieve long-term survival after curative surgery [20, 29–31]. Therefore, there are currently no widely accepted treatment guidelines for CY1P0 GC patients.

Based on the above background, we designed this study, aiming to evaluate the safety and efficacy of perioperative SOX plus sintilimab with/without preoperative CRT. The study protocol of this trial, which has the acronym NeoRacing, is described in this article.

## Methods

### Study design

NeoRacing is a randomized phase II trial carried out at Fudan University Shanghai Cancer Center (FUSCC) in China. The study can be divided into the screening stage, treatment stage and follow-up stage. The enrolled patients will receive perioperative SOX chemotherapy, PD-1 antibody (sintilimab) and radical surgery, with or without preoperative CRT (Fig. 1). The patients were randomized by stratified permutated block randomization on a web-based system. The status of peritoneal cytological examination (CY0 vs. CY1) was the stratification factor. The study protocol was approved by the Ethics Committee of FUSCC. All patients provided written informed consent before recruitment. Monitoring will be carried out in this trial.

**Fig. 1 Fig1:**
[figure not shown]
Flow chart of the NeoRacing study

### Primary endpoint

The primary endpoint is the pathological complete regression (pCR) rate: the proportion of patients who achieve pCR after preoperative therapy. Patients with a CY0 status at the time of enrollment should have no residual tumor cells in the primary lesion and the dissected lymph nodes in the surgical specimens (ypT0N0M0). Patients with a CY1 status at the time of enrollment should reach both ypT0N0M0 and a CY0 status.

### Secondary endpoints

The pathological response rate (pRR) is defined as the proportion of patients with pathological response. The tumor regression will be evaluated according to Ryan’s tumor regression grading (TRG) [32]. The pathological response is defined as TRG0 and TRG1 of the primary lesion after preoperative therapy.The R0 resection rate is defined as the proportion of patients who achieve R0 resection. For patients with a CY0 status at the time of recruitment, the tumor should be completely removed, and no residual tumor cells within 1 mm of the resection margin should be confirmed by postoperative pathology. For patients with a CY1 status at the time of recruitment, an extra requirement is that CY0 should be confirmed by a peritoneal cytological examination.The objective response rate (ORR) is defined as the proportion of patients with a complete response (CR) or a partial response (PR) to preoperative therapy. The ORR will be evaluated using the RESIST1.1 protocol.Event-free survival (EFS)Overall survival (OS)Treatment safetySurgical complications

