### Inclusion criteria

Histopathologically confirmed gastric adenocarcinoma (G) or gastroesophageal junction adenocarcinoma (GEJ, excluding Siewert type I).The clinical stage of the enrolled patients was cT3-4aN + M0 or cT4bNanyM0. Patients with a CY1 status but no other distant metastasis were allowed for patient recruitment. The clinical stage of CY1 patients is cT3-4aN + M1 (CY1 only) or cT4bNanyM1 (CY1 only) (the 8th AJCC staging system of GC).The tumor was considered to be potentially resectable, which was verified by a multidisciplinary team including a surgical investigator.At least one evaluable lesion on abdominal CT/MRI according to the RESIST 1.1 protocol is required.An ECOG (Eastern Cooperative Oncology Group) performance status of 0-1.The patient’s physical state and organ function can tolerate the planned treatment of the study protocol, including perioperative chemotherapy with the SOX regimen and immunotherapy with PD-1 monoclonal antibody, preoperative concurrent chemoradiotherapy (45 Gy/25 fractions/S-1), and major abdominal surgery.The baseline laboratory examinations of the patients met the following criteria:An adequate hematological function: an absolute neutrophil count (ANC) ≥ 1.5 × 10^9^/L; a platelet count ≥100 × 10^9^/L; a hemoglobin level ≥ 90 g/L.Adequate liver function: total bilirubin ≤1.5 × upper limit of normal (ULN); AST/ALT < 2.5 × ULN; ALP ≤ 2.5 × ULN; ALB ≥30 g/L.Adequate renal function: serum creatinine ≤1.5 × ULN; creatinine clearance rate ≥ 60 ml/min.Adequate coagulation function: INR/PT ≤ 1.5 × ULN; APTT ≤1.5 × ULN.There was no serious concomitant disease, and the patient’s life expectancy was more than 6 months.Male or female. Age ≥ 18 years and ≤ 75 years.Patients agreed to sign a written informed consent before recruitment.Patients had good compliance with the study procedures, including laboratory examinations, auxiliary examinations and treatment.The female patients should not be pregnant or breastfeeding.The female patients agreed to take contraceptive measures during the treatment and within 120 days after the last dose of PD-1 mAb or 180 days after the last dose of chemotherapy or radiotherapy.

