
### Treatment arms

During the screening stage, patients with LAGC or GEJ adenocarcinoma will undergo baseline examinations, including enhanced CT scans of the stomach, pelvic cavity and chest (if necessary). After preliminary screening, patients who may meet the inclusion criteria will receive laparoscopic exploration or laparotomy, and all of them will receive abdominal exfoliative cytology concurrently. Patients without gross peritoneal seeding (P0) will be finally enrolled. Eligible patients were randomized to two arms: the arm of perioperative ChT and ICI with preoperative CRT (Arm A) and the arm of perioperative ChT and ICI (Arm B).

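### The R0 definition asks for negative peritoneal cytology only from patients who were CY1 at entry, so a patient found CY1 at surgery after CY0 at entry can count as R0

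*Protocol article*

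**What the plan says.** Under Secondary endpoints, the protocol article gives the R0 rule in two branches, chosen by cytology at recruitment.

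- CY0 at recruitment: "the tumor should be completely removed, and no residual tumor cells within 1 mm of the resection margin should be confirmed by postoperative pathology". No cytology condition is named.
- CY1 at recruitment: the same conditions, with one addition: "For patients with a CY1 status at the time of recruitment, an extra requirement is that CY0 should be confirmed by a peritoneal cytological examination".

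Elsewhere the article says what a positive cytology means. The Background says that CY1 without gross peritoneal disease "is a special type of distant metastasis of GC, which is defined as stage IV disease". The Inclusion criteria stage it accordingly: "The clinical stage of CY1 patients is cT3-4aN + M1 (CY1 only) or cT4bNanyM1 (CY1 only". Cytology for every patient is described at the exploration during screening (Treatment arms: "all of them will receive abdominal exfoliative cytology concurrently"), and the result is used in randomization (Study design: "The status of peritoneal cytological examination (CY0 vs. CY1) was the stratification factor").

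The primary endpoint has a similar split. Patients who were CY0 at enrollment need ypT0N0M0. For the others, "Patients with a CY1 status at the time of enrollment should reach both ypT0N0M0 and a CY0 status".

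**The concern.** An endpoint that describes the result of surgery should depend on what is found at surgery. Here the cytology condition applies or not according to a test done before any treatment. Two patients with the same operative result (tumor removed, margin clear, cytology positive) are scored differently because of their screening result. One of them is scored as a success while carrying what the article calls metastatic disease.

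Two things are at stake. R0 does not mean the same in the two strata, so a pooled R0 rate mixes two definitions. And in the CY0 stratum the rate can be overstated by the patients whose cytology has turned positive, or whose screening lavage was falsely negative.

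**Working it through.** The article states no figure for the R0 rate, so there is none to reproduce. The sample size rests on pCR and is not touched by this point. The check is a comparison of the wording, followed by an illustration of scale.

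**Step 1: apply the rule to each case.** Take patients whose tumor was completely removed with a clear 1 mm margin. The CY0 confirmation asked of CY1 patients must come from a cytology later than the entry one, since the entry result was positive.

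| Cytology at entry | Cytology at surgery | R0 as worded | R0 under one rule |
|---|---|---|---|
| CY0 | CY0 | yes | yes |
| CY0 | CY1 | **yes** | **no** |
| CY0 | not done | yes | yes |
| CY1 | CY0 | yes | yes |
| CY1 | CY1 | no | no |

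Only the second row changes. It disagrees with the last row although the surgical finding is the same.

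**Step 2: compare with the article's own staging.** Background and Inclusion criteria both place CY1 in the metastatic category (stage IV, M1). The second row therefore credits an R0 resection to a patient who is M1 by the article's staging.

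**Step 3: does the same hold for pCR?** The CY0 branch of the primary endpoint requires ypT0N0M0. With CY1 staged as M1, a patient known to be CY1 at surgery is not M0 and so does not meet it. The CY1 branch names CY0 in addition to ypT0N0M0, which makes the wording somewhat redundant and leaves room for doubt, but M0 already implies the exclusion.

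**Step 4: scale, on assumptions only.** Let q be the share of patients who are CY0 at entry and c the share of those who are CY1 at surgery. The most patients per arm that the second row can hold is 76 × q × c, where 76 is the planned number per arm (Sample size calculation).

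- q is not given. The Discussion reports that about one-third of potentially eligible patients in the PREACT trial were P1 or CY1. P1 is excluded here, so if that mix carried over, q would be at least about two-thirds. I take 70% to 90%.
- c is not given and nothing in the documents bounds it. I take 2% to 10% purely for illustration.

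| q | c | 76 × q × c | Points of the R0 rate (100 × q × c) |
|---|---|---|---|
| 0.70 | 0.02 | 1.1 | 1.4 |
| 0.80 | 0.05 | 3.0 | 4.0 |
| 0.90 | 0.10 | 6.8 | 9.0 |

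For each pair of assumptions these are upper bounds. They suppose that every patient is resected, is otherwise R0, and has cytology at surgery.

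**The case against.** The strongest reply is that the CY0 branch also demands complete removal. If CY1 is metastatic disease, a patient known to be CY1 at surgery arguably fails that condition, and the added requirement merely asks for proof of conversion from patients already known to be positive. No sentence says outright that a patient who goes from CY0 to CY1 is R0. This stands as far as it goes: the outcome follows from the wording and is not a declared rule. But if complete removal already covered free peritoneal cells, the added requirement for CY1 patients would be redundant. Moreover, the confirmation named in the CY0 branch is postoperative pathology of the margin, not cytology.

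A reader might go further and infer three things that the documents do not support.

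- *That pCR is miscounted in the same way.* The M0 term, with CY1 staged as M1, already excludes such patients. Only the clarity of the wording is open.
- *That the rule hides or creates a difference between the arms.* Nothing shows that conversion differs by arm. Stratified randomization balances entry cytology, so with equal conversion both R0 rates would be overstated by about the same amount. Balance at entry does not guarantee equal conversion, but a difference is not shown. Event-free survival also counts peritoneal seeding and distant metastasis in both arms.
- *That CY0 patients have no cytology at surgery.* The article describes cytology for all patients at screening and is silent on a repeat in this stratum. That is procedural detail which an article may leave to the full protocol, so its absence is not established.

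**Conclusion.** The point holds for the R0 definition. As worded, a patient who was CY0 at entry and CY1 at surgery can be counted as R0, against the article's own classification of CY1 and against its treatment of the same finding in the other stratum. This is a fault in a rule that is written out for both strata, not an omission due to condensing.

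The number of patients affected is unknown. The illustration of about 1 to 7 of 76 per arm depends entirely on assumed values of q and c and should not be read as an estimate. The point concerns one secondary endpoint, leaves the sample size unchanged, and for the primary endpoint calls only for clearer wording. It is a minor correction.

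**What to change.** In Secondary endpoints, state one rule for both strata: any positive peritoneal cytology found at surgery means not R0, whatever the cytology at entry. Keep the existing demand that patients who were CY1 at entry have CY0 confirmed. Report, by stratum, how many patients had cytology at surgery, so that readers can see how far the R0 rate was verified in each.

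In Primary endpoint, add a short clarification that M0 in ypT0N0M0 excludes CY1.

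No added lavage procedure is part of this change. The cost is one sentence in the R0 definition, a clause in the pCR definition and one line in the results. The R0 rate may be slightly lower. A limit remains: if not every CY0 patient has cytology at surgery, some conversions stay undetected and are still counted as R0, which is why the number tested should be reported.

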### Explorative endpoints

The association of the baseline PD-L1 comprehensive positive score (CPS), tumor mutation burden (TMB), mismatch repair (MMR) status, and EBER with the efficacy of immunotherapy will be assessed.The association between the gut microbiota and the efficacy of immunotherapy will be assessed.The association between the *Helicobacter pylori* (HP) infection status and the efficacy of immunotherapy will be assessed.The influence of the preoperative therapy on the tumor immune microenvironment (TIME) and the systemic immune status will be assessed.

### Inclusion criteria

Histopathologically confirmed gastric adenocarcinoma (G) or gastroesophageal junction adenocarcinoma (GEJ, excluding Siewert type I).The clinical stage of the enrolled patients was cT3-4aN + M0 or cT4bNanyM0. Patients with a CY1 status but no other distant metastasis were allowed for patient recruitment. The clinical stage of CY1 patients is cT3-4aN + M1 (CY1 only) or cT4bNanyM1 (CY1 only) (the 8th AJCC staging system of GC).The tumor was considered to be potentially resectable, which was verified by a multidisciplinary team including a surgical investigator.At least one evaluable lesion on abdominal CT/MRI according to the RESIST 1.1 protocol is required.An ECOG (Eastern Cooperative Oncology Group) performance status of 0-1.The patient’s physical state and organ function can tolerate the planned treatment of the study protocol, including perioperative chemotherapy with the SOX regimen and immunotherapy with PD-1 monoclonal antibody, preoperative concurrent chemoradiotherapy (45 Gy/25 fractions/S-1), and major abdominal surgery.The baseline laboratory examinations of the patients met the following criteria:An adequate hematological function: an absolute neutrophil count (ANC) ≥ 1.5 × 10^9^/L; a platelet count ≥100 × 10^9^/L; a hemoglobin level ≥ 90 g/L.Adequate liver function: total bilirubin ≤1.5 × upper limit of normal (ULN); AST/ALT < 2.5 × ULN; ALP ≤ 2.5 × ULN; ALB ≥30 g/L.Adequate renal function: serum creatinine ≤1.5 × ULN; creatinine clearance rate ≥ 60 ml/min.Adequate coagulation function: INR/PT ≤ 1.5 × ULN; APTT ≤1.5 × ULN.There was no serious concomitant disease, and the patient’s life expectancy was more than 6 months.Male or female. Age ≥ 18 years and ≤ 75 years.Patients agreed to sign a written informed consent before recruitment.Patients had good compliance with the study procedures, including laboratory examinations, auxiliary examinations and treatment.The female patients should not be pregnant or breastfeeding.The female patients agreed to take contraceptive measures during the treatment and within 120 days after the last dose of PD-1 mAb or 180 days after the last dose of chemotherapy or radiotherapy.

### Exclusion criteria

Clinical or histopathological evidence of peritoneal seeding (P1) or distant metastasis (M1).Patients who have previously received surgery, chemotherapy, radiotherapy or immunotherapy for gastric cancer.Patients had a history of cancer in the five years before randomization except for squamous or basal cell carcinoma of the skin that had been effectively treated and superficial bladder cancer, cervical carcinoma in situ and breast cancer in situ that had been treated by surgery.Pregnant or lactating females or planning to become pregnant or lactating.History of allergy to any drugs involved in this study.History of allogeneic stem cell transplantation or organ transplantation.Vaccinated with a live vaccine within 4 weeks before recruitment.History of anti-PD-1, PD-L1, PD-L2 or any other specific T cell costimulation or checkpoint pathway targeted therapy.History of using steroids (dose > 10 mg/d prednisone) or other systemic immunosuppressive therapy within 14 days before recruitment, except for patients treated with the following regimen: steroids used for hormone replacement (dose > 10 mg/d prednisone); local application of steroids with little systemic absorption; short-term (≤ 7 days) use of steroids to prevent allergy or vomiting.Patients with weight loss of more than 20% within 2 months before recruitment.Uncontrolled systemic diseases, including diabetes and hypertension.Failure of important organs (heart, lung, liver, kidney, etc.).Moderate or severe renal injury [creatinine clearance ≤50 ml/min (according to Cockroft & Gault equation)] or SCR > ULN.Dipyrimidine dehydrogenase (DPD) deficiency.Patients with central nervous system (CNS) disorders, peripheral nervous system disorders or psychiatric diseases.A cerebrovascular accident that occurred within 6 months before recruitment.Patients with a known history of uncontrolled or symptomatic angina, uncontrolled arrhythmias and hypertension, congestive heart failure, cardiac infarction within 6 months prior to study recruitment, or cardiac insufficiency.Patients who have the following history of pulmonary diseases: interstitial lung disease, noninfectious pneumonia, pulmonary fibrosis, acute lung disease, or pulmonary embolism.Patients with severe gastrointestinal bleeding, gastrointestinal perforation, or gastrointestinal fistula and patients who cannot swallow to take the drug orally.Patients with upper gastrointestinal obstruction, dysfunction or malabsorption syndrome that can affect the absorption of oral chemotherapy drugs.Uncontrollable pleural effusion, pericardial effusion, or ascites that occurred within two weeks before recruitment.Patients with a history of active autoimmune disease or refractory autoimmune disease.Severe chronic or active infections requiring systemic antibiotics, antifungal or antiviral therapy, including tuberculosis and AIDS.Known history of human immunodeficiency virus (HIV) infection.Patients with untreated chronic hepatitis B or HBV-DNA exceeding 500 IU/ml or HCV-RNA positivity.
